### Study variables

#### Result variables

##### Clinical efficacy of prebiotic/probiotic dietary modulation

-Scale for Positive and Negative Schizophrenia Syndrome (45) (categorized PANSS): discrete.-Personal and Social Functioning Scale (46) (categorized PSP) outcome: discrete.

##### Tolerability and modulation of the nutritional dietary pattern

-Food Frequency Questionnaire (FFQ) (47) result: continuous-Culinary knowledge and responsibility for feeding: nominal.

##### Anthropometric variables and physical health

Weight (kg, continuous), height (cm, continuous), BMI (kg/m^2^, continuous) abdominal circumference (cm, continuous), systolic blood pressure (mmHg, continuous), diastolic blood pressure (mmHg, continuous), heart rate (ppm, discrete).

##### Blood test variables

-*Hematological profile*: Red blood cells (x10e^6^/mm^3^, continuous), hemoglobin (g/dL, continuous), hematocrit (%, continuous), M.C.V. (fL, discrete), H.C.M. (pg, discrete), C.H.C.M. (g/dL, discrete), R.D.W (%, continuous), leukocytes (×10e^3^/mm^3^, discrete), neutrophils (×10e^3^/m, continuous), lymphocytes (×10e^3^/m, continuous), monocytes (×10e^3^/m, continuous), eosinophils (×10e^3^/m, continuous), basophils (×10e^3^/m, continuous), platelets (×0e^3^/mm^3^, discrete), M.P.V. (fL, discrete). See Table 1 for abbreviations corresponding to the blood test variables.

**TABLE 1 T1:** Blood test variables: Abbreviations.

	Abbreviation	Meaning
Hematological profile	M.C.V	Mean corpuscular volume
	H.C.M	Mean corpuscular hemoglobin
	M.C.H.C	Mean corpuscular hemoglobin concentration
	R.D.W	Red cell distribution width
	M.P.V	Mean platelet volume
Biochemical profile	ALT	Alanine transaminase
	GPT	Glutamic pyruvic transaminase enzyme
	G-GT	Gamma-glutamyl transferase
	ALP	Alkaline phosphatase
	Na^+^	Sodium
	K^+^	Potassium
	Cl^–^	Chlorine
	Ca^2+^	Calcium
	HbA1c	Glycosylated hemoglobin
	IFCC	International federation of clinical chemistry and laboratory medicine
	Fe^2+^	Iron
	FRT	Ferritin
	LDH	Lactate dehydrogenase
	C-HDL	High-density lipoprotein
	C-LDL	Low-density lipoprotein
	TSH	Thyroid stimulating hormone
	PRL	Prolactin
	LUES	Syphilis
	HCV	Hepatitis C virus
	HAV	Hepatitis A virus
	HIV	Human immunodeficiency virus

-*Biochemical profile.* ALT/GPT (IU/L, discrete), G-GT (IU/L, discrete), FAL (IU/L, discrete), Na^+^/K^+^ (mEq/L, discrete/continuous, respectively), Cl^–^ (mEq/L, continuous), Ca^2+^ (mEq/L, continuous), urate (mg/dL, continuous), glucose (mg/dL, discrete), HbA1c (%, continuous), HbA1c IFCC (mmol/mol, continuous), fructosamine (mcmol/L, discrete), creatinine (mg/dL, continuous), Fe^2+^ (mcg/dL, discrete), FRT (mcg/dL, discrete), folate (mcg/dL, continuous), vit.B12 (ng/mL, discrete), vit.D total (D2 + D3) 25-OH (ng/mL, discrete) cholesterol (mg/dL, discrete), triglycerides (mg/dL, discrete), LDH (IU/L, discrete), C-HDL (mg/dL, discrete), C-LDL (mg/dL, discrete), total cholesterol/C-HDL (mg/dL, discrete), glomerular filtrate estimation (mL/m/173, discrete), TSH (mU/L, continuous), PRL (ng/dL, continuous), LUES (IU/L, nominal/discrete), a-HAV-M (IU/L, nominal/discrete), a-HCV (IU/L, nominal/discrete), HBsAg (UI/L, nominal/discrete), a-HBC-IgG (UI/L, nominal/discrete), a-HBs (UI/L, continuous), a-HIV (mcL, nominal/discrete).

#### Stool variables

##### Stool culture

General bacteriology. Usual mixed flora: Lactobacillus (CFU/g, continuous), Bifidobacterium (CFU/g, continuous)//Disbiosis: *Salmonella* spp. (nominal, Presence/absence), *Shigella* spp. (nominal, presence/absence), *Yersinia* spp. (nominal, presence/absence), Hafnia alvei (nominal, presence/absence), *Aermonas* spp. (nominal, presence/absence), *Campylobacter* spp. (nominal, presence/absence).

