### Statistical analysis

Quantitative variables will be presented with mean and standard deviation, and qualitative variables will be shown in frequencies and percentages.

The Kolmogorov-Smirnov test will be used to compare the goodness of fit to a normal distribution of data from quantitative variables. For the contrast of bivariate hypotheses, the Student *t*-test will be performed for two means, while for qualitative variables, the Chi-Square and Fisher’s exact test will be used, when necessary. Likewise, for the analysis of three or more means, the ANOVA of repeated means will be used. On the other hand, the correlation between quantitative variables will be verified through the Pearson’s coefficient r. When the normality or homoscedasticity criteria are not met, non-parametric versions of the above tests will be performed.

Logistic regressions will be carried out to determine which variables can determine the improvement of the nutritional pattern and physical health through the FFQ (47), as well as blood and stool analytical values. Similarly, this analysis will be established concerning the psychopathological status through the PSP (46) and PANSS (45) scales, both of which have a discrete quantitative and nominal result values, according to established cut-off points and clinical interpretation. Raw and adjusted odds ratios will be calculated. Log-likelihood, the goodness of fit statistic, Cox and Snell R2, Nagelkerke R2, and Hosmer-Lemeshow tests should be used to assess the overall model fit. The exponentiation will be used to calculate the beta coefficients.

These multivariate tests will allow us to identify and adjust for the possible confounding effect of the independent variables on the outcome variables.

For all statistical analyses, an alpha error probability of less than 5% (*p* < 0.05) will be accepted, and the confidence interval will be calculated at 95%. The software SPSS (version 25.0) and EPIDAT (version 4.2) shall be used for the statistical analysis.

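### Lactobacillus and Bifidobacterium counts should be analysed and reported as log10 CFU/g adjusted for baseline, not as raw means and SDs with a rank-test fallback

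*Protocol article*

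**What the plan says.** Under Stool culture, the protocol article lists "Lactobacillus (CFU/g, continuous), Bifidobacterium (CFU/g, continuous". The other organisms in that section are recorded as present or absent, so these two counts are the only quantitative measures of the microbiota. Under Study design, stool is sampled at baseline and at 6 months.

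Statistical analysis sets one rule for all such variables:

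- Summary: "Quantitative variables will be presented with mean and standard deviation".
- Normality check: "The Kolmogorov-Smirnov test will be used to compare the goodness of fit to a normal distribution of data from quantitative variables".
- Two groups: Student's t-test. Correlation: Pearson's r.
- Fallback: "When the normality or homoscedasticity criteria are not met, non-parametric versions of the above tests will be performed".
- Models: logistic regressions giving raw and adjusted odds ratios, which draw on the FFQ "as well as blood and stool analytical values". The form in which the counts enter (raw, log or cut-off) is not stated.

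**The concern.** Bacterial counts usually vary by multiples rather than by fixed amounts. When they do, the arithmetic mean and SD on the CFU/g scale mostly describe the highest few participants. A reader of the results table could not tell from them whether the diet moved the typical participant's count, or by how much.

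The fallback changes the test and leaves the summary alone. A rank test yields a p-value; the plan attaches no effect estimate to it, and it takes no account of where each participant started, although the baseline sample is taken anyway. The trial is meant to work by modulating the microbiota, so these two variables should be reported with an interpretable effect.

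**Working it through.** **The plan's own figure.** Selection of participants gives 11 per arm for a risk difference of 63 points at 80% power and 95% confidence. The usual two-proportion formula, two-sided, with rates of 63% and 0%, gives

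(1.96 × √(2 × 0.315 × 0.685) + 0.8416 × √(0.63 × 0.37))² / 0.63² = 7.2 per arm.

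The continuity correction raises this to 10.2, so 11. Over all rate pairs 63 points apart, the corrected answer is 11 or 12. The stated 22 is reproduced to within two patients and does not depend on the scale of the counts.

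**Inputs for the counts.** From the document: 25 per arm, baseline and 6-month samples, alpha 5% (taken as two-sided). Assumed, because the document gives no spread: normal log10 counts with SD σ from 0.5 to 1.0, a true shift of 0.8σ, and a correlation of 0.5 between baseline and 6 months.

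**Step 1: the raw mean and SD.** For log-normal counts the ratio of SD to mean is √(exp((2.3026σ)²) − 1). The shares are from simulation at 25 per arm.

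| σ | SD ÷ mean | Median share of arm total, largest value | Same, two largest |
|---|---|---|---|
| 0.5 | 1.7 | 20% | 33% |
| 0.75 | 4.3 | 32% | 50% |
| 1.0 | 14.1 | 42% | 63% |

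**Step 2: does the fallback fire?** At 25 per arm, Kolmogorov-Smirnov on the pooled raw counts rejects normality in 95% of simulated trials at σ = 0.5 and in essentially all at 0.75 and above. The plan's rule therefore nearly always ends in the rank test.

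**Step 3: power at 25 per arm.** The basic quantity is 0.8 × √(25/2) = 2.83.

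- Plan's rule, ending in a rank test: 2.83 × √(3/π) = 2.76, and Φ(2.76 − 1.96) = 79%. Simulation of the full rule gives 76–77%.
- t-test on log10 counts: Φ(2.83 − 1.96) = 81%; 79–80% with the t distribution and in simulation.
- log10 counts adjusted for baseline: the shift becomes 0.8/√(1 − 0.5²) = 0.924 residual SDs, and 0.924 × √12.5 = 3.27, so Φ(3.27 − 1.96) = 90%; about 88–89% with the t distribution and in simulation.

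The log scale alone adds about 2–4 points. Baseline adjustment adds about 9 or 10 more.

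**Step 4: the effect that would be reported.** At σ = 1.0 the true ratio is 10^0.8 = 6.3. In simulation the ratio of raw arm means runs from about 0.6 to above 60 (central 95% of trials), and in 6% of trials the arm with the truly higher counts has the lower mean. The baseline-adjusted log10 difference has standard error 1.0 × √0.75 × √(2/25) = 0.245, so its central 95% range is 0.8 ± 0.48, a ratio of about 2.1 to 19. At σ = 0.5 the true ratio is 10^0.4 = 2.5, and the ranges are about 1.1 to 5.8 for raw means and 10^0.16 to 10^0.64, or 1.4 to 4.4, for log10.

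**The case against.** A reader might infer that one or two participants would decide the microbiota test itself, or that power collapses. A t-test forced onto raw counts would have about 56% power at σ = 0.5 and about 22% at σ = 1.0. The protocol does not support that reading. Its fallback sends such data to a rank test in almost every trial of the planned size, and extreme values do not dominate ranks. The fallback follows the sentence on Pearson's r and so covers correlations too.

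The gain of about 10 points or more should not be credited to the log scale: most of it is baseline adjustment, and it depends on the assumed correlation. Figures at 11 per arm look worse, but that is the calculated minimum; the planned size is 25 per arm.

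The stakes are limited. The main objective is nutritional and cardio-metabolic, and the dysbiosis items are nominal. The article does not say that a difference in raw means will be the effect estimate; the only effect measure it names is the odds ratio.

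It can also be said that a log transformation is a detail an article may leave to a fuller plan. That holds for detection limits and table layout. It does not remove the point, because the article positively fixes mean and SD for quantitative variables without exception and names a rank test as the alternative.

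**Conclusion.** The point holds as a matter of summary, effect size and efficiency, and not as a threat to the validity of the test. If the counts are strongly skewed, the stated mean and SD rest heavily on the largest values, and the fallback supplies neither an interpretable effect nor use of the baseline count. Under the stated assumptions, the change raises power at 25 per arm from about 76–79% to about 88–89%. The spread, the shift and the correlation are all assumed; with a narrower spread the reporting problem shrinks, and with a weaker baseline correlation the power gain does. How far the logistic models are affected cannot be judged, since the form of the counts there is not stated. Sample size, alpha and the presence/absence items are unaffected. Importance is minor to moderate.

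**What to change.** Name log10(CFU/g) as the analysis scale for both counts, with a stated value for counts below detection. Compare the arms at 6 months by a linear model on log10 counts with arm and baseline log10 count as terms. Report geometric means by arm and the between-arm ratio with its 95% CI, in place of the raw mean and SD. Use the log10 values wherever the counts enter a correlation or regression, and say so.

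This needs no extra samples, visits or participants: it is a transformation and a covariate already collected. If a fuller analysis plan already does this, one sentence confirming it is enough.

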### Independent variables

#### Sociodemographic variables

Age (continuous), gender (nominal), legal representative (nominal), household composition (nominal), economic level (ordinal), level of studies (ordinal), area of residence (nominal).

#### Therapeutic variables

Previous antipsychotic (nominal), the dose of antipsychotic (mg, continuous), the reason for a change in antipsychotic treatment (nominal).

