### Selection of participants

For the assessment of the method’s effectiveness, a sample size of 22 individuals has been estimated (11 for the IG and 11 for the CG, with a power of 80% and a confidence of 95%, expecting a risk/prevalence difference of 63% post-intervention (48). The final size of 50 individuals has been established (25 for the IG and 25 for the GC) to minimize the effect of possible losses and the low study completion rates, especially in participants with significant negative symptoms. Participants who express a clear wish to participate voluntarily in the study will be assigned, through randomization in balanced blocks, to the IG or CG (Figure 1). Randomization will be conducted according to the results found in stool culture analysis (balancing the prevalence of dysbiosis in both groups). Concerning the established inclusion/exclusion criteria, these will be:

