#### Inclusion criteria

-Patients diagnosed on the spectrum of schizophrenia (without distinction by type), according to criteria DSM-5 and/or ICD-11.-Age between 18 and 65 years.-Absence of gastrointestinal comorbidity that contraindicates the use of prebiotics and/or probiotics (intolerance, explosive diarrhea, acute abdominal pain, etc.).-To show clinical stability for 6 months before the start of the study (absence of psychiatric hospitalization, maintenance of the level of functionality, and lack of social and occupational absenteeism).-To manifest agreement to participate in the study and to sign of informed consent (Supplementary Appendices I–III).

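### Antipsychotic dose is defined in raw milligrams across different drugs, so any odds ratio or correlation for dose mixes drug identity with treatment intensity

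*Protocol article*

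**What the plan says.** Under Independent variables, the Therapeutic variables section of the protocol article lists three items:

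- "Previous antipsychotic (nominal")
- "the dose of antipsychotic (mg, continuous")
- "the reason for a change in antipsychotic treatment (nominal")

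The Statistical analysis section plans logistic regressions to find which variables determine improvement in diet, physical health and psychopathology. It states: "Raw and adjusted odds ratios will be calculated". It adds: "These multivariate tests will allow us to identify and adjust for the possible confounding effect of the independent variables on the outcome variables". It also plans Pearson correlations between quantitative variables, and dose as defined is one of these.

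Eligibility does not limit the drug. The Inclusion criteria admit "Patients diagnosed on the spectrum of schizophrenia (without distinction by type"), and neither they nor the Exclusion criteria name an antipsychotic. The article mentions no conversion to a common dose scale, no standardisation within drug and no drug-by-dose term.

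**The concern.** A regression with one continuous mg variable fits one slope per milligram for everybody. That slope has a common meaning only if a milligram represents the same treatment intensity in every patient. Here the drug is a nominal variable and switches are anticipated, so several drugs are expected. A patient on a drug given in large mg amounts then counts as highly exposed even when treated lightly, and the reverse.

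Two things are at stake. First, a reported effect of dose on an outcome such as lipids, weight or PANSS could be an effect of drug choice. Second, the plan treats dose as a possible confounder, and its Justification section refers to iatrogenic metabolic syndrome in psychiatric patients. With 25 per arm, chance imbalance in treatment intensity is possible, and a covariate that tracks intensity poorly removes little of it while appearing to deal with it.

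**Working it through.** **Figures in the plan.** No figure in the article depends on the dose variable. The sample size ("11 for the IG and 11 for the CG, with a power of 80% and a confidence of 95"%) rests on a 63-point difference in proportions. The arm rates are not given. With the lower rate varied from 0 to 0.37, a two-sided 5% test, 80% power and a continuity correction, the formula gives 11 to 12 per arm. The stated figure is therefore reproduced, and the dose scale plays no part in it.

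**Model for raw mg.** The article names no drugs, doses or drug mix, so these inputs are assumptions:

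- Raw mg = f × I. Here f is the drug's mg per unit of intensity, and I is relative intensity (the equivalent dose), lognormal with mean 1 and log SD s, independent of drug.
- Two drugs, equally used, with f = 1 and f = R.
- CV² of I = exp(s²) − 1. With s = 0.4 this is exp(0.16) − 1 = 0.1735, so CV = 0.4165.

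Formulas:

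- Between-drug variance B = ((R − 1)/2)²
- Within-drug variance W = ((1 + R²)/2) × CV²
- Share of mg variance due to drug identity = B/(B + W)
- Correlation of mg with equivalent dose = ((1 + R)/2) × CV / √(B + W)

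Twofold ratio: B = 0.25 and W = 2.5 × 0.1735 = 0.434. Share = 0.25/0.684 = 37%. Correlation = 1.5 × 0.4165/0.827 = 0.76.

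Tenfold ratio: B = 20.25 and W = 50.5 × 0.1735 = 8.76. Share = 20.25/29.01 = 70%. Correlation = 5.5 × 0.4165/5.386 = 0.425, about 0.43.

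| Potency ratio R | Share due to drug (s = 0.4) | Correlation with equivalent dose (s = 0.4) |
|---|---|---|
| 2 | 37% | 0.76 |
| 3 | 54% | 0.61 |
| 5 | 64% | 0.50 |
| 10 | 70% | 0.43 |
| 100 | 74% | 0.37 |

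**Sensitivity.** A wider spread of dose within drug lowers the share: at R = 10 with s = 0.6 it is 48%, with correlation 0.56. A simulation used five equally used drugs, spaced evenly on the log scale, with within-drug CV of 0.3 / 0.5 / 0.7. The drug share was:

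- 38% / 19% / 10% over a twofold range
- 80% / 59% / 42% over a tenfold range
- 86% / 70% / 53% over a fiftyfold range

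On a common scale (R = 1) the share is 0% and the correlation is 1, by construction.

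**Effect on the arm comparison.** A simulated logistic model used 50 patients, drug factors 1, 3, 30 and 100, s = 0.4, and an assumed strong effect of 0.8 log-odds per SD of log dose. The false-positive rate for treatment stayed near 5% whether the model used raw mg or equivalent dose. At a treatment log odds ratio of 1.5, power was about 0.61 unadjusted, 0.61 to 0.63 with raw mg, and 0.66 to 0.67 with equivalent dose. In that setting, using raw mg gives up most or all of a gain of about five points.

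**The case against.** The strongest reply is that the Therapeutic variables section is a list of what is collected, and mg is a proper unit for recording a dose. Deriving analysis variables is commonly left to a fuller document. No sentence names dose as a covariate in any particular model, and with 50 patients the many independent variables listed could not all be entered together. Allocation is also randomised.

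Much of this stands. A reader might infer that raw mg enters every adjusted model; the article gives no covariate list, so that is not established. What it does do is place dose, with its unit and type fixed, under the heading whose variables it will use to "identify and adjust for the possible confounding effect of the independent variables on the outcome variables". The scale is a stated choice, and it makes dose a candidate on that scale.

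A reader might also infer that the variable mostly measures which drug is taken. That holds for some assumed drug mixes and fails for others, such as a twofold potency range, so the article does not support it as a general statement. Nor is it shown that the dose coefficient would take a spurious sign, or that patients on high-mg drugs would have extreme leverage. Bias in the treatment comparison does not follow either, because randomisation protects it.

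Adding the nominal drug variable would not answer the point. Drug indicators absorb differences in level but still force one per-mg slope on all drugs, and many indicators are hard to support with 50 patients. The only drug variable listed is also labelled as the previous antipsychotic, so it may not be the drug to which the dose belongs.

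**Conclusion.** The point holds in a limited, conditional form. If dose is used as defined, its odds ratio and its correlations have no common meaning across drugs, and adjustment for treatment intensity is weakened. The size cannot be fixed from the article. Under the two-drug assumptions above (equal use, s = 0.4), between a twofold and a tenfold potency ratio, drug identity accounts for about 37% to 70% of the variance of raw mg, and the correlation with equivalent dose falls from 0.76 to 0.43. Drugs of similar mg potency, or a wide dose spread within drug, make the problem smaller.

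The consequences are confined to the search for determinants, the dose correlations and a modest loss of precision in adjusted models. The unadjusted comparison of the arms and the sample size stand. This is an inexpensive improvement to the analysis and does not threaten the trial's main comparison.

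**What to change.** Keep recording the drug and its dose in mg, and make three changes:

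1. Make sure the drug to which the recorded dose belongs is captured. If the variable for the previous antipsychotic is meant to be that drug, relabel it; if not, add the current drug.
2. In any correlation or regression, replace raw mg with baseline dose converted to one common scale named in advance, for example the ratio to the defined daily dose. If a participant takes more than one antipsychotic, sum the converted doses.
3. State in the analysis section that this derived variable, and not raw mg, is the candidate covariate. The baseline value precedes the intervention, so adjusting for it cannot remove part of the intervention's effect.

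The cost is one derived variable, a sentence or two of analysis text, and possibly one data field for the current drug. It is an analysis variable only: treatment, visits and sample size do not change.

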#### Clinical variables

Type of psychotic disorder (nominal), duration of illness (continuous), age of first hospitalization (continuous), number of previous hospitalizations (discrete), number of previous relapses (discrete), number of previous suicidal behaviors (discrete), number of subsequent hospitalizations (discrete), number of subsequent relapses (discrete), number of subsequent suicidal behaviors (discrete), number of subsequent unscheduled consultations (discrete), substance abuse (nominal), type of substance (nominal), associated cardio-metabolic diagnosis (nominal).

Anthropometric measurements will be collected following the recommendations of the Manual of Standardized Anthropometry (49). Weight, height, and BMI shall be measured with an SECA^®^ 703s stadiometer and scale, with an accuracy of 0.1 kg and 0.1 cm, respectively. The abdominal perimeter shall be determined at the midpoint between the last rib and the iliac crest at the end of a normal expiration. The WelchAllyn^®^ ProBP 2,400 digital sphingomanometer shall be used for the study of blood pressure and heart rate.

